# Transperineal prostate brachytherapy, using I-125 seed with or without adjuvant androgen deprivation, in patients with intermediate-risk prostate cancer: study protocol for a phase III, multicenter, randomized, controlled trial

**DOI:** 10.1186/1471-2407-10-572

**Published:** 2010-10-21

## Abstract

**Background:**

The optimal protocol for ^125^I-transperineal prostatic brachytherapy (TPPB) in intermediate-risk prostate cancer (PCa) patients remains controversial. Data on the efficacy of combining androgen-deprivation therapy (ADT) with ^125^I-TPPB in this group remain limited and consequently the guidelines of the American Brachytherapy Society (ABS) provide no firm recommendations.

**Methods/Design:**

Seed and Hormone for Intermediate-risk Prostate Cancer (SHIP) 0804 is a phase III, multicenter, randomized, controlled study that will investigate the impact of adjuvant ADT following neoadjuvant ADT and ^125^I-TPPB. Prior to the end of March, 2011, a total of 420 patients with intermediate-risk, localized PCa will be enrolled and randomized to one of two treatment arms. These patients will be recruited from 20 institutions, all of which have broad experience of ^125^I-TPPB. Pathological slides will be centrally reviewed to confirm patient eligibility. The patients will initially undergo 3-month ADT prior to ^125^I-TPPB. Those randomly assigned to adjuvant therapy will subsequently undergo 9 months of adjuvant ADT. All participants will be assessed at baseline and at the following intervals: every 3 months for the first 24 months following ^125^I-TPPB, every 6 months during the 24- to 60-month post-^125^I-TPPB interval, annually between 60 and 84 months post-^125^I-TPPB, and on the 10th anniversary of treatment.

The primary endpoint is biochemical progression-free survival (BPFS). Secondary endpoints are overall survival (OS), clinical progression-free survival, disease-specific survival, salvage therapy non-adaptive interval, acceptability (assessed using the international prostate symptom score [IPSS]), quality of life (QOL) evaluation, and adverse events. In the correlative study (SHIP36B), we also evaluate biopsy results at 36 months following treatment to examine the relationship between the results and the eventual recurrence after completion of radiotherapy.

**Discussion:**

These two multicenter trials (SHIP0804 & SHIP36B) are expected to provide crucial data regarding the efficacy, acceptability and safety of adjuvant ADT. SHIP36B will also provide important information about the prognostic implications of PSA levels in intermediate-risk PCa patients treated with ^125^I-TPPB.

**Trial registration:**

NCT00664456, NCT00898326, JUSMH-BRI-GU05-01, JUSMH-TRIGU0709

## Background

Studies show improved outcomes when androgen-deprivation therapy (ADT) is included in the therapeutic regimen for men with intermediate-risk prostate cancer [1], and available data provide stronger support for the benefits of ADT than for those of radiation dose escalation in patients with intermediate-risk disease [1]. In order to obtain further gain, five phase III clinical trials (RTOG0232, RTOG0815, NCT00890006, NCT00388804, NCT00005044) examining combined use of external beam radiation (EBRT) and ADT in intermediate-risk patients are being planned or currently in progress [2,3].

^125^I-transperineal prostatic brachytherapy (TPPB) was added to the Japanese armamentarium for treatment of localized PCa in 2003 [4]. Since then, more than 5,000 patients have undergone this procedure. However, the indication for brachytherapy in intermediate-risk patients remains controversial. TPPB alone is considered inadequate for these patients due to possible extraprostatic extension. Retrospective studies have suggested that ADT can improve outcomes in intermediate-risk PCa patients treated with TPPB [1]. There are, however, no reported prospective studies documenting the effectiveness of adjuvant ADT with TPPB for intermediate-risk patients. Such prospective clinical trials are clearly needed. In the present paper, we describe our study protocol for a phase III, multicenter, randomized, controlled study of TPPB with or without adjuvant ADT in patients with intermediate-risk PCa.

Adjuvant ADT is significantly associated with adverse events. The PROST-QA study prospectively measured patient-reported quality of life outcomes before and after prostate cancer treatment [5]. Sexual function was persistently worse among radiation patients who received ADT than among those who did not. Vitality and other outcomes related to hormonal therapy (e.g., fatigue, weight change, gynecomastia, depression, and hot flashes) were also worse in the ADT patients. Furthermore, symptoms persisted after radiotherapy for up to two years despite < 1 year of ADT [5]. Thus, patients at intermediate risk who already face the dilemma of choosing between treatment modalities have their choice further complicated by the adverse event profile of ADT and recommending this therapy may not be appropriate until we have firmer evidence of its benefit. The present trial (SHIP0804) is also expected to provide crucial data regarding acceptability (assessed using the international prostate symptom score [IPSS]) and quality of life (QOL).

For assessment of PCa treatment efficacy, biochemical failure is a rational early endpoint. Numerous investigators in the PSA era have demonstrated the importance of biochemical outcome following treatment. A definition of PSA nadir level + 2 ng/mL, which is adopted in the present study, was recently proposed as the recommended definition of biochemical failure [6]. This definition reduces misinterpretation of unstable PSA status, such as that due to the bounce phenomenon, and eliminates backdating of progression to preceding measurements.

On the other hand, it was previously reported that the correlation between biopsy results at 6-36 months after completion of radiotherapy and the eventual development of recurrence after completion of radiotherapy was highly significant retrospectively [7]. In a correlative study (SHIP36B), the relationship between PSA levels and biopsy results 36 months after treatment will be investigated. SHIP36B will also provide important information about the prognostic implications of PSA levels in intermediate-risk PCa patients treated with TPPB.

As mentioned above, the optimal protocol for ^125^I-transperineal prostatic brachytherapy (TPPB) in intermediate-risk prostate cancer (PCa) patients remains controversial. In the present paper, we describe our study protocols for a phase III, multicenter, randomized, controlled study of TPPB with or without adjuvant ADT in patients with intermediate-risk PCa (SHIP0804), and to examine the relationship between PSA levels and biopsy results 36 months after treatment (SHIP36B).

## Methods/Design

### Aim of the study

To examine the effect of adjuvant luteinizing hormone-releasing hormone-agonist (LHRHa) therapy (SHIP0804) and to examine biopsy results at 36 months after brachytherapy (SHIP36B) for intermediate-risk PCa patients who have received 3-month neoadjuvant LHRHa followed by ^125^I-TPPB.

### Study design

The present investigation is a phase III, multicenter, randomized, controlled study of ADT and TPPB for patients with untreated intermediate-risk PCa (Figure 1). All patients are randomized to one of two treatment arms in which patients either do or do not receive 9-month adjuvant therapy with a LHRHa following ^125^I-TPPB. Prior to ^125^I-TPPB, all patients undergo 3-month LHRHa therapy, which consists of subcutaneous goserelin acetate, 3.6 mg/mo, or leuprolide acetate, 3.75 mg/mo. In a correlative study (SHIP36B), the relationship between PSA levels and biopsy results 36 months after treatment will be investigated.

**Figure 1 F1:**
[figure not shown]
**Study design of SHIP0804 and SHIP36B. ADT, androgen deprivation therapy, TPPB, transperineal prostatic brachytherapy**.

### Additional measures

Two validated QOL questionnaires, the SF-8™, which has been translated into Japanese and is stored in the PBRN database (SQL Server 7.0), and the Expanded Prostate Cancer Index Composite (EPIC), will be administered to comprehensively cover the various aspects of physical and psychosocial well-being.

### Site selection

For an institution to participate, the institution's attending physicians must:

a. Acquire certified documentation of participation in the Japanese Brachytherapy Scientific Meeting's training session for the ^125^I-TPPB procedure.

b. Have experience with ^125^I-TPPB in at least 50 patients.

c. Regularly perform ^125^I-TPPB procedures.

### Eligibility criteria - Exclusion criteria

Patients are ineligible if they:

a. Have previously received surgery for PCa.

b. Have PSA > 20 ng/mL.

c. Have a biopsy Gleason score ≥ 8.

e. Exhibit clinical stage ≥ T2c.

f. Have a second cancer that requires treatment.

g. Have poorly-controlled hypertension (diastolic pressure ≥ 120 mmHg)

h. Have a severe psychiatric disorder, including schizophrenia and dementia.

i. Have poorly-controlled diabetes.

j. Are using steroid drugs other than topical ointments.

k. Are using antiandrogenic therapy.

l. Are for any other reason considered by a Principal Investigator or Clinical Investigator to be inappropriate for participation in the present study.

### Informed Consent - Ethics Approval

The study was conducted in accordance with the Helsinki Declaration of 1975, as revised in 2000. All treatments for PCa are undertaken following written informed consent, and further consent is obtained for procedures to confirm the diagnosis of intermediate-risk category. This study received approval from the Foundation for Biomedical Research and Innovation, Translational Research Informatics Center (TRI) ethical review committee (approval No. 07-05, date Feb 8, 2008) and the institutional ethics committees of the participating facilities.

### Methods of recruitment and random allocation

Recruitment of patients is supported by the Seed and Hormone for Intermediate-risk Prostate Cancer Study Group (SHIP). Recruiting began in April, 2008, and is planned for completion by March, 2011. Initial recruitment is through the secretariat division of SHIP. All prostatic biopsy histological slides of newly diagnosed PCa since the study was initiated have been reviewed by central pathologists, with patient eligibility being determined at the time of review. Eligible patients are randomly assigned to one of two treatment arms through the data center at the TRI. Randomization is done centrally using a minimization method to obtain good between-group balance for factors including age category (< 70/≥ 70), PSA category (< 10/≥ 10 ng/mL) and institutions.

### Central review of the pathological diagnosis

Following enrolment of the patients, biopsy specimens are collected and forwarded to the central pathology group for review. Three uropathologists review the pathology specimens and classify each according to the modified Gleason grading system proposed by the International Society of Urological Pathology (ISUP) [10]. All cases are reviewed independently without clinical information and decisions are made by consensus.

### Technique of ^125^I-TPPB

^125^I-TPPB for all patients is administered using an ultrasound-guided technique with the Mick applicator [4]. The implant is planned to deliver a dose of at least 144Gy to the clinical target volume, which includes the prostate gland and treatment margin [11]. Although individual technical aspects are institution-dependent, efforts are made to assure optimal quality control of the radiation dose. Computed tomography images, taken at 2-5 mm intervals, are obtained one month after ^125^I-TPPB to determine the extent of edema. Dose-volume histograms for the prostate, urethra, and rectum are computed to obtain post-planning distribution data. V100 and D90 should be over 95% and 144Gy respectively for the clinically targeted volume [11,12]. We organized a quality control committee for this study with the aim of assessing inter-institutional variance of post-implant dosimetry. This board will meet regularly while this protocol is running to monitor and compare dosimetry. Results of the comparative analysis will be reported separately.

### Data collection

This design was chosen to ensure accurate, standardized and high-quality data collection. All patients giving written informed consent to the study are asked to complete a short family history and epidemiology questionnaire. Electronic Data Capture (EDC) systems are used to collect clinical data in electronic format, with clinical data being obtained from patient medical records by the TRI. A follow-up data form is completed by the Clinical Trials Practitioner (CTP) at diagnosis, 3 months, 6 months, 9 months, 12 months, 15 months, 18 months, 21 months, 24 months, and then every 6 months until 60 months post-treatment, after which forms are completed annually until 84 months from the date of ^125^I seed implantation. These forms capture information regarding patient characteristics, disease presentation, diagnosis and treatment, PSA, recurrence and survival. Annual follow up is continued until death, loss to follow up or the end of the active phase of the study (March, 2021).

### Definition of endpoints

The primary endpoint is biochemical progression-free survival (BPFS). Biochemical progression is defined as an increase in prostate specific antigen (PSA) of 2 ng/mL or greater from the nadir value following treatment. Secondary endpoints include OS, clinical progression-free survival (local, distant failure), disease-specific survival, salvage therapy non-adaptive interval, acceptability (assessed by the international prostate symptom score [IPSS]), quality of life (QOL) and adverse events. Overall survival and progression-free survival are respectively calculated from the 1st day of treatment to any death, or to identification of disease progression or death. Local progression is defined as reappearance of local tumorat the primary site. Reappearance of local tumor will be confirmed by rectal examination and imaging studies such as magnetic resonance imaging or computed tomography. The primary endpoint of a correlative study (SHIP36B) is the biopsy results at 36 months following treatment to examine the relationship between results and eventual recurrence after completion of radiotherapy.

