### Planned statistical analyses

It has been shown that the 5-year BPFS rate ranges from 63% to 98% in patients with intermediate-risk PCa who undergo radiotherapy [13,14]. Assuming that the 7-year BPFS rate of the control group is 60% (the 5-year BPFS is about 69%) and the expected 7-year BPFS rate of the adjuvant ADT group is 73.6% (i.e. hazard ratio is 0.6), 190 patients for each group are needed to detect a significant difference between treatments by log-rank test with a significance level of 0.05 and a power of 80%. Given the further assumption that approximately 10% of randomized patients will be unevaluable for various reasons, the target sample size was set at 210 patients per group (420 patients total).

Statistical analyses will be performed on an intention-to-treat basis. Survival curves will be estimated using the Kaplan-Meier method. To test for differences in survival curves between the two groups of patients, the log-rank test will be used. The hazard ratio will be estimated using the Cox proportional hazard model. The longitudinal change of QOL scores (IPSS, SF-8, and EPIC) between diagnosis and 60 months following ^125^I-TPPB will also be compared between groups. Patients will be evaluated for toxicity, graded according to the National Cancer Institute Common Toxicity Criteria version 3.0 [15]. For all patients, the incident proportion of grade 3 adverse events will be compared between groups by Fisher exact test. All tests will be two-sided, and a value of 0.05 will be considered statistically significant. Five years after the last patient is recruited, an interim analysis will be performed and the results will be reported to the Independent Data Monitoring Committee.

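### Survival is timed from an undefined first day of treatment, which cannot be applied to every randomised patient and does not fit the stated intention-to-treat analysis

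*Protocol article*

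**What the plan says.** Under *Definition of endpoints*, the protocol article sets the clock for overall and progression-free survival: they are "calculated from the 1st day of treatment to any death" for the former, and to progression or death for the latter. It does not say whether the first day of treatment is the first LHRH-agonist dose or the seed implantation. BPFS is the primary endpoint. The quoted sentence does not name it, but BPFS and clinical progression-free survival are the only progression-free endpoints listed, and no separate origin is given for either.

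Under *Planned statistical analyses*: "Statistical analyses will be performed on an intention-to-treat basis". The same section inflates the sample size because "approximately 10% of randomized patients will be unevaluable for various reasons"; it does not define the term.

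On sequence, *Methods of recruitment and random allocation* states: "Eligible patients are randomly assigned to one of two treatment arms through the data center at the TRI". The eligibility criteria require previously untreated patients. The abstract puts treatment after enrolment and randomisation: "The patients will initially undergo 3-month ADT prior to ^125^I-TPPB", and then "Those randomly assigned to adjuvant therapy will subsequently undergo 9 months of adjuvant ADT".

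**The concern.** An intention-to-treat comparison needs an endpoint that can be computed for every randomised patient from a point that allocation cannot influence. The date of randomisation meets both needs. The first day of treatment exists only for patients who reach it, and it falls after the allocation is known. A patient who withdraws or dies in between has no survival time under the stated rule, and his events are not covered.

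Care is identical in both arms up to the implant, so the treatment-based origin should not bias the comparison among patients who start. That says nothing about those who do not start. Allocation comes first, no blinding is described, and only one arm faces nine further months of androgen deprivation, whose side effects the *Background* says complicate patients' choices. Withdrawal before the start could therefore differ by arm. Leaving such patients out would then be a post-randomisation selection related to allocation.

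**Working it through.** **1. Who has no time zero.**

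| Meaning of first day of treatment | Randomised patients without a time zero |
|---|---|
| First neoadjuvant dose | Those who never start any treatment |
| Seed implantation | Those above, plus anyone who leaves during the 3-month neoadjuvant phase |

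The text supports either meaning. The abstract places neoadjuvant therapy first in the treatment sequence. However, its visit schedule runs from the implant, and *Data collection* uses post-treatment times on a schedule that ends 84 months after implantation. Under both meanings the group without a time zero can be non-empty, while intention-to-treat requires that it be analysed.

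**2. The plan's own figure.** Inputs from *Planned statistical analyses*: 7-year BPFS 60% and 73.6%, two-sided 0.05, power 80%.

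- Hazard ratio: ln(0.736)/ln(0.60) = 0.600, as stated.
- Freedman events: (1.960 + 0.842)² × (1.6/0.4)² = 7.85 × 16 = 125.6, so 126.
- Mean 7-year event probability: (0.40 + 0.264)/2 = 0.332.
- Patients: 126/0.332 = 379.5, or 190 per group. This reproduces the plan.
- Allowance: 190 × 1.1 = 209 and 190/0.9 = 211; the stated 210 lies between.

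Moving the origin to randomisation changes none of these inputs.

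**3. Possible bias if non-starters were left out.** The document gives no never-start rate, so these rates are assumptions. Let a share q never start in the adjuvant arm and q/2 in the control arm, let these patients have k times the usual hazard, and let there be no true effect. After exclusion the adjuvant arm has hazard 1 and the control arm has [(1 − q) + (q/2)k]/(1 − q/2). The apparent hazard ratio is the inverse of the latter.

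- q = 0.10, k = 2: 0.95/(0.90 + 0.10) = 0.95.
- q = 0.10, k = 0.5: 0.95/(0.90 + 0.025) = 1.03.
- q = 0.02, k = 2: 0.99/(0.98 + 0.02) = 0.99.
- q = 0.02, k = 0.5: 0.99/(0.98 + 0.005) = 1.005.

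**4. What keeping everyone does to power.** Freedman power is Φ(√d × (1 − HR)/(1 + HR) − 1.96), with d events. Suppose a share x never starts, and those in the adjuvant arm have the control outcome (assumption). If kept, that arm's 7-year BPFS is (1 − x) × 0.736 + x × 0.60, HR = ln(BPFS)/ln(0.60), and d = 420 × (0.40 + 1 − BPFS)/2. If a share x of all 420 is dropped, HR stays at 0.6 and d = 420 × (1 − x) × 0.332.

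| x | Dropped: events, power | Kept: HR, events, power |
|---|---|---|
| 2% | 136.7, 83% | 0.607, 140.0, 82% |
| 5% | 132.5, 82% | 0.618, 140.9, 80% |
| 10% | 125.5, 80% | 0.637, 142.3, 75% |

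The case for the change is validity, not power.

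**The case against.** The strongest reply is that the article states intention-to-treat without qualification and nowhere says that non-starters are dropped. It is also a condensed account, so their handling may be set out in the full protocol or analysis plan. This stands as far as exclusion goes: a reader might infer that such patients fall out of the primary analysis, but the document does not say so. It does not remove the conflict, because the origin is stated explicitly rather than left out, and as stated it cannot be applied to everyone randomised.

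It can also be said that unequal withdrawal before the start is speculative. Both arms begin with the same treatment, and a patient unwilling to take adjuvant therapy can start the common part and decline later, after time zero, when intention-to-treat keeps him in his arm. This too stands: unequal loss is possible but not shown, and if the clock starts at the first dose few patients are likely to be affected.

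Two stronger readings are tempting and should be resisted.

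- A reader might take the 10% unevaluable allowance as evidence that the plan expects losses before treatment. The text gives only unspecified reasons. Loss to follow-up or a central pathology finding after enrolment would fit equally well. The term needs reconciling with intention-to-treat, but it does not count non-starters.
- A reader might expect that analysing all 420 raises power from 80% to 84% (420 × 0.332 = 139.4 events at HR 0.6). That holds the hazard ratio at 0.6 while adding back patients who did not receive the adjuvant therapy. If 5% of the adjuvant arm has the control outcome the gain is gone, and at 10% power is about 75%.

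**Conclusion.** The point holds as an unreconciled conflict between a stated time origin and a stated analysis principle. It reaches BPFS by implication, since no other origin is given, although the sentence does not name it. It is made worse because the first day of treatment is not defined.

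The effect is likely small. Even the assumed 10% versus 5% never-start rates move a null hazard ratio only to between 0.95 and 1.03, against a design value of 0.6. At 2% versus 1% the range is 0.99 to 1.005. These rates and the hazard multipliers of 0.5 to 2 are assumptions; the document gives neither a never-start rate nor the interval from randomisation to first treatment. The 190 and 210 per group are unaffected. The change is worth making because it is cheap and protects the randomised comparison, not because the trial's conclusion is shown to be at risk.

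**What to change.** - Time BPFS, overall survival and the other time-to-event endpoints from the date of randomisation.
- Keep every randomised patient in the allocated arm, including those who never start, censored at the last PSA or contact if event-free.
- State how biochemical progression is assessed when there is no post-treatment nadir. The present definition counts a rise from the nadir after treatment, which an untreated patient does not have, so moving the origin alone does not define BPFS for him.
- Define unevaluable and reconcile it with intention-to-treat.
- Define the first day of treatment, and keep the treatment-start or implant origin as a sensitivity analysis.

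Cost: a short paragraph of text. Randomisation is central, so the date should already be held. Times lengthen slightly by the gap between randomisation and treatment, and non-starters dilute the effect slightly (HR about 0.607 if 2% of the adjuvant arm has the control outcome). The visit schedule runs from the implant, so follow-up of patients who never reach it needs a line as well.
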